### Sample size

Using data from a previous study recording functional outcomes, the mean WOMAC score at 2 years using MA TKA was 26 (standard deviation 22.6) and using TKA with kinematic alignment was 15 (standard deviation 20.3) [14]. Using a two-tailed, two-sample *t* test with an effect size of 0.35, power of 90% with significance level of 5%, and accounting for an expected drop-out rate of 10% during the 2-year follow-up period, the study requires 100 patients to detect a minimal clinically important difference of 11 points in the total WOMAC score between the two treatment groups [13].

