### Statistical analysis

The analysis of the per-protocol population will be considered the primary analysis. The differences between the MA TKA and FA TKA groups will be analysed by calculating the difference from baseline per patient, and a two-sided confidence interval for the difference between the changes from baseline values will be calculated. This confidence interval will cover the true difference in the percentage change from baseline with a probability of 95%. The following statistical methods will be employed to analyse the data: descriptive statistics, independent *t* test, paired *t* test, analysis of variance, Fisher exact test, chi-square test and graphical displays. Assumptions of normality will be tested with the D’Agostino test. Assumptions of homogeneity of variance will be tested with Levene’s test. If the distributional assumptions are (severely) violated, non-parametric techniques such as the Mann–Whitney test will be employed. In the event that FA TKA is converted to MA TKA intraoperatively, analysis will be performed using the intention-to-treat population and the treatment actually received by the patients. Intraoperative conversion from FA TKA to MA TKA will be documented and presented and published as part of the study. Statistical significance is set at a *P* value <0.05 for all analyses and all statistical analyses will be performed using SPSS software version 25 (SPSS Inc., Chicago, IL, USA). The Bonferroni correction will be used to adjust *P* values to reduce the risk of type I error with performing multiple statistical comparisons.

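### The Bonferroni rule names no family and does not say that the single primary endpoint, sized at an unadjusted two-sided 5%, is left out of it

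*Protocol article*

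**What the plan says.** The Objectives section names one primary comparison: total WOMAC, mechanical against functional alignment, at 2 years. The Sample size section plans it as follows: "Using a two-tailed, two-sample *t* test with an effect size of 0.35", "power of 90% with significance level of 5" per cent, 100 patients in all, "to detect a minimal clinically important difference of 11 points in the total WOMAC score between the two treatment groups". No allowance for multiplicity enters that calculation.

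The Statistical analysis section plans a two-sided 95% confidence interval for the between-group difference in change from baseline, sets P < 0.05 as the threshold for all analyses, and ends by saying that the Bonferroni correction will adjust P values "to reduce the risk of type I error with performing multiple statistical comparisons". It names no family and no number of comparisons, and it neither includes nor exempts the primary endpoint.

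The Outcomes section lists twelve outcome items. They include eight questionnaires (seven patient-reported scores plus EQ-5D), each recorded at four postoperative visits. WOMAC is one of the eight, and its 2-year value is not set apart from its other visits.

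**The concern.** A Bonferroni correction multiplies each P value by the number of comparisons in the family. Until that number and its members are fixed, the rule cannot be carried out. Two things are at stake.

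First, if an analyst counts the 2-year WOMAC test among the multiple comparisons, the primary is tested at 0.05/k, although it was sized at 0.05 and will be reported with a 95% interval. The interval could then exclude zero while the adjusted P value is above 0.05.

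Second, even if the primary is left alone, the secondary family stays open within this text. WOMAC, KOOS and OKS overlap heavily and are measured repeatedly, so the choice of which results share a correction decides which are called significant.

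**Working it through.** **Inputs, all from the Sample size section unless stated**

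- Mechanical alignment: "the mean WOMAC score at 2 years using MA TKA was 26 (standard deviation 22.6").
- Kinematic alignment: "using TKA with kinematic alignment was 15 (standard deviation 20.3").
- Difference to detect: 11 points. Test: two-sided t test at 5%. Power: 90%. Dropout: 10%.
- 100 patients at 1:1 with 10% dropout leave 90 evaluable, or 45 per arm.
- k, the size of the Bonferroni family, is **not given**. I take 2 to 60 as an assumed range. Two points inside it can be counted from the article: 10 (the primary plus the nine secondary objectives) and 32 (eight questionnaires × four postoperative visits).

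**Step 1. Standardised difference.** Pooled SD = √[(22.6² + 20.3²)/2] = 21.48, so d = 11/21.48 = 0.512. The article's own phrase is "with an effect size of 0.35", which does not match.

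**Step 2. The plan's own figure.** At d = 0.512, two-sided 5% and 90% power, 82 evaluable patients per arm are needed: 164 in all, and 164/0.9 = 183 with dropout. At the stated 0.35 it is 173 per arm: 346, or 385 with dropout. Neither gives 100. This shortfall is independent of multiplicity and must be kept apart from it.

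**Step 3. Power with and without Bonferroni.** The noncentrality parameter is d√(n/2) = 0.512 × √22.5 = 2.43, on 88 degrees of freedom. Power is the noncentral-t probability beyond the two-sided critical value at 0.05/k.

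| k | level | power, 45 per arm | power, 50 per arm (no dropout) |
|---|---|---|---|
| 1 (unadjusted) | 0.0500 | 67% | 72% |
| 2 | 0.0250 | 56% | 61% |
| 10 | 0.0050 | 33% | 38% |
| 32 | 0.0016 | 21% | 25% |
| 60 | 0.0008 | 16% | 20% |

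**Step 4. What Bonferroni alone costs.** In a trial that truly had 90% power at 5%, testing at 0.05/k would leave 84% at k = 2, 67% at k = 10 and 53% at k = 32.

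**Step 5. A check with a very small k.** Suppose the trial observes exactly 11 points with these SDs and 45 per arm. The standard error is 21.48 × √(2/45) = 4.53, t = 11/4.53 = 2.43, P = 0.017, and the 95% interval is 2.0 to 20.0. Multiplied by 3, P = 0.052. Three comparisons would be enough to make the target difference non-significant while its 95% interval excludes zero.

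**Limit of the check.** The SDs are those of 2-year scores, whereas the Statistical analysis section analyses change from baseline, whose SD is not given. With equal SDs at both times it would be 21.48 × √[2(1 − r)], which is below 21.48 only if the baseline to 2-year correlation r exceeds 0.5. The article does not state r.

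**The case against.** A reader might infer that the plan contradicts itself: that, as written, the primary P value is multiplied by the number of comparisons. The text does not support this. The phrase about all analyses belongs to the 0.05 threshold, not to the Bonferroni sentence, and a Bonferroni-adjusted P value is itself compared with 0.05, so the two sentences are compatible. One endpoint at one time point, sized at 5% and reported with a 95% interval, fits most naturally with an unadjusted primary test. That stands, and it is why this is an ambiguity.

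A reader might also quote a power of 20% to 35% as what the plan delivers. No k is written, so that range follows only from assuming about 9 to 36 comparisons with 45 per arm. Nor may the whole fall from 90% be charged to Bonferroni, since the step from 90% to 67% comes from the sample size.

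It can further be said that the family is a detail for the analysis plan, which is not shown and may settle it. That lowers the weight of the point but does not remove it: the article does commit to a multiplicity rule, and that rule cannot be applied as stated. Finally, Bonferroni is valid under any correlation between outcomes, so its conservatism is not an error. Preferring Holm is an improvement, not a correction.

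**Conclusion.** The point holds as an ambiguity in a stated rule. The protocol article commits to Bonferroni without naming the family and without saying that the primary endpoint, sized at an unadjusted two-sided 5%, lies outside it.

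If the primary were included, power for 11 points would drop from 67% to somewhere between 56% (k = 2) and 16% (k = 60). This assumes 45 evaluable patients per arm, the 2-year SDs and an assumed k. If the primary is excluded, which is the more coherent reading, its power is untouched by this rule, and what remains is the undefined secondary family. The shortfall from 90% to 67% is a different error and is not part of this point. I class this as a cheap improvement.

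**What to change.** Replace the Bonferroni sentence with three statements:

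1. *Total WOMAC at 2 years is the single primary endpoint and is tested at two-sided 5% without adjustment for multiplicity.* This matches the level used for sizing and the planned 95% interval.
2. *The secondary family is [a named list, for example the other patient-reported scores at 2 years]; its P values are adjusted by Holm's method.* Holm controls the same familywise error as Bonferroni under any correlation and is never less powerful.
3. *All other outcomes and visits are reported as estimates with 95% confidence intervals.*

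The cost is wording in the protocol or analysis plan, fixed before the data are unblinded. Recruitment, data collection and patient management do not change. The downside is that outcomes outside the named family become descriptive and cannot be called significant. This change does not restore the planned 90% power, which needs separate attention to the sample size.

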## Methods/design

### Objectives

The primary objective of this study is to compare the total Western Ontario and McMaster Universities Arthritis Index (WOMAC) score in MA TKA versus FA TKA at 2 years after surgery. As FA TKA enables improved restoration of native, patient-specific knee kinematics [15, 26, 29], the study hypothesis is that total WOMAC scores will be superior in patients undergoing FA TKA compared to MA TKA at 2 years follow-up.

The secondary objectives are to compare the following outcomes between the two treatment groups:
Accuracy of implant positioning and limb alignmentSurgical efficiencyPostoperative functional rehabilitationFunctional outcomesQuality of lifeImplant migrationGaitResource use and cost-effectivenessComplications

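### P values are to be adjusted by Bonferroni; Holm's step-down version gives the same error control, never rejects less, and would be a free but usually small gain

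*Protocol article*

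**What the plan says.** The Statistical analysis section of the protocol article names one multiplicity method, the Bonferroni correction of P values, "to reduce the risk of type I error with performing multiple statistical comparisons". The same section states: "Statistical significance is set at a *P* value <0.05 for all analyses". It does not list the comparisons in the family, count them, or limit the correction to secondary outcomes. It plans a two-sided 95% confidence interval for the difference in change from baseline and does not say that intervals will be adjusted for multiplicity.

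The Objectives section names one primary outcome, total WOMAC at 2 years, and continues: "The secondary objectives are to compare the following outcomes between the two treatment groups". Nine domains follow, from accuracy of implant positioning to complications. The Outcomes section shows that several of these domains contain more than one measure, most of them recorded at repeated visits. The Sample size section claims power for the primary outcome only.

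**The concern.** Without further qualification, a Bonferroni correction means the single-step version: every P value is compared with the family-wise level divided by the number of tests. Holm's step-down version gives the same guarantee with thresholds that are never stricter. For P value adjustment alone, the planned method therefore cannot do better than Holm and can do worse.

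At stake is some power on the secondary comparisons. Many of them are overlapping patient-reported measures of the same knee. If functional alignment works as hypothesised, several should move together, and Holm helps most when many outcomes differ. With about 45 evaluable patients per arm, secondary power after adjustment is low in any case, so an improvement that costs nothing is worth taking.

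**Working it through.** **No planned figure to reproduce.** The article gives no number for the multiplicity procedure, so the check compares the two methods directly.

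**Why Holm is never worse.** Let there be m tests with ordered P values p(1) ≤ … ≤ p(m), and a family-wise level of 0.05.

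- Bonferroni rejects each hypothesis with p ≤ 0.05/m.
- Holm compares p(j) with 0.05/(m − j + 1), starting at j = 1, and stops at the first failure.
- Since 0.05/(m − j + 1) ≥ 0.05/m at every step, Holm rejects everything that Bonferroni rejects. For m = 9 Bonferroni's threshold is 0.0056 throughout; Holm's run 0.0056, 0.0063, 0.0071 and so on up to 0.05.
- Holm's error control: with m0 true null hypotheses, the first of them to be rejected falls at step m − m0 + 1 or earlier, so its P value is at most 0.05/m0. Summing over the m0 true nulls bounds the family-wise error by 0.05, whatever the correlation.
- Holm's first threshold equals Bonferroni's, so Holm rejects something only when Bonferroni does.

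**Inputs for the size of the gain.**

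- From the article: 100 patients, 1:1 allocation and 10% drop-out, giving 50 × 0.9 = 45 per arm; two-sided 5%.
- Assumed: nine tests (one per listed domain), pairwise correlation 0.5, normal test statistics, and a common effect of 0.5 SD. For orientation, the article's WOMAC figures (means 26 and 15, SDs 22.6 and 20.3) give a pooled SD of √[(22.6² + 20.3²)/2] = 21.48 and an effect of 11/21.48 = 0.512.
- A smaller effect of 0.35 SD is also shown. It is the value in the Sample size section ("Using a two-tailed, two-sample *t* test with an effect size of 0.35"), used here only as a lower case.

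**Bonferroni by formula.** Non-centrality is 0.5 × √(45/2) = 2.37. The critical value for a two-sided 0.05/9 is 2.77. Power is P(Z > 2.77 − 2.37) = P(Z > 0.40), about 34%. At 0.35 SD, non-centrality is 0.35 × √(45/2) = 1.66, and power is P(Z > 1.11), about 13%.

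**Bonferroni v Holm by simulation** (nine tests, 45 per arm, correlation 0.5):

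| True effects among nine | Effect | Bonferroni, power per true effect | Holm |
|---|---|---|---|
| 1 | 0.5 SD | 34–35% | the same |
| 3 | 0.5 SD | 34% | 36% |
| 5 | 0.5 SD | 34% | 37% |
| 9 | 0.5 SD | 34% | 42% (42–43% between runs) |
| 9 | 0.35 SD | 13% | 16% |

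With no true effects the family-wise error is about 4% for both methods.

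**Sensitivity** (same design, effect 0.512 SD):

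- Nine tests, all true, zero correlation: 36.5% v 43.4%.
- Twenty tests, correlation 0.5: 27.4% v 28.4% with six true, and 27.6% v 34.7% with all twenty true.
- Chance of at least one true rejection, nine tests, correlation 0.5: 61.0% v 61.0% with three true, and 80.4% v 80.4% with all nine true.

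**The case against.** The strongest reply is that nothing here is wrong. Bonferroni is prespecified, holds the error it is meant to hold under any dependence, and conflicts with nothing else in the article. On this view, preferring Holm is a matter of taste. Validity is conceded. But when one valid procedure never rejects less than the other at the same error level, naming it is an improvement, not only a preference.

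The family is also assumed. The article does not restrict the correction to secondary outcomes or count the tests, and the nine items in the Objectives section are domains. This stands, so the percentages above are illustrations. That Holm never rejects less holds for any family and any number of tests.

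The largest gain needs all nine outcomes to differ by half an SD. That is unlikely for a list that includes complications, resource use, and accuracy of positioning when both arms use the same robot. This stands too: with a minority of outcomes truly different, the gain is 0 to 2 points.

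Finally, Bonferroni has simple matching simultaneous intervals and Holm does not. That would matter if the plan used them. It applies the correction to P values and describes ordinary 95% intervals.

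A reader might go further and infer that the plan needlessly loses power on every secondary outcome, or that real differences will be missed as a result. The article does not support that. Holm gains only once Bonferroni has already rejected something, the gain is nil with a single true effect, and no power is claimed for any secondary outcome.

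**Conclusion.** This is a minor point: an available improvement to a valid plan. Holm holds the same 5% family-wise error without extra assumptions and never rejects less. Under the stated assumptions, the gain in power per true effect runs from nothing with one true effect to about 8 points with all nine; at 0.35 SD it reaches only about 3 points with all nine. The chance of finding at least one true difference hardly changes.

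The ordering of the two methods is mathematical. The sizes rest on an assumed number of tests, correlation and effect, none of which the article gives for the secondary outcomes. Whether the primary WOMAC comparison belongs in the corrected family is a separate question.

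**What to change.** In the Statistical analysis section, replace the Bonferroni correction by the Holm step-down adjustment for the multiple secondary comparisons. Make the change before any unblinded results are seen. Report the Holm-adjusted P values beside the unadjusted 95% confidence intervals already planned, and label the intervals as unadjusted.

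The cost is one line of text. The adjusted values follow from the raw P values by hand: order them, multiply the j-th smallest by (m − j + 1), carry the running maximum forward, and cap at 1. No extra data or patients are needed. The small downside is the lack of equally simple simultaneous intervals, which the plan does not promise.

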### Adverse events

Adverse events are defined as any untoward medical occurrence in a patient or study participant that does not necessarily have a causal relationship with the procedure involved. A serious adverse event (SAE) is an adverse event that results in hospitalisation or prolongation of existing hospitalisation, persistent or significant disability or incapacity, life-threatening clinical sequelae, or death. All SAEs during the protocol treatment will be reported directly to the sponsor using the SAE web form. The chief investigator will also assess the SAE for severity, causality, seriousness and expectedness using pre-existing criteria provided by the sponsor and will inform the Data Safety Monitoring Board (DSMB) within 3 days of the initial observation of the event. The protocol treatment period is defined as the period from the day that the first study patient is recruited into the trial to the day that the final study patient has completed 2 years follow-up. The chief investigator will also inform the London-Surrey Research Ethics Committee and local Health Research Authority within 3 days of the SAE taking place. Safety aspects of the study are closely monitored by the sponsor and DSMB using unblinded data for its judgment. In cases where the SAE arises due to a problem with the robotic device, Stryker Limited will also be notified within 2 days of the event taking place. The chief investigator will record the following: onset date, complete description of the event, severity, duration, action taken and outcome for each SAE. The chief investigator will also provide regular updates of all SAEs to the London-Surrey Research Ethics Committee, local Health Research Authority, DSMB, and sponsor.

### Data management

On-site monitoring visits shall occur throughout the course of the clinical study by the chief investigator. The chief investigator shall permit and assist the sponsor (should they chose to monitor the study) to carry out verification of all study forms against data in the source documents, which shall occur as per the departmental policy for undertaking such activities. University College Hospital recognises that there is an obligation to archive study-related documents at the end of the study. The study master file will be archived at University College London in accordance with the University College Hospital Standard Operating Procedure for Archiving of Investigator Site File and Pharmacy Site File. It will be archived for a minimum of 5 years from the study end, and for no longer than 30 years from the study end.

### End-of-protocol treatment

Reasons for going off study protocol include:
Completion of last follow-up visit 2 years after surgeryPatient non-compliance or withdrawal (the reason for discontinuation will be recorded in the case report form)Intercurrent death

All patients included in this study are free to withdraw from the study at any time without compromise to their future treatment. On withdrawal, patients will revert to the standard follow-up regimen for routine (non-study) TKA at the study site. The end-of-study form will be completed and the reason for withdrawal documented. This form will also be completed if the patient is lost to follow-up or dies during the course of the study. Data to the point of discontinuation will be used for analysis.

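### The 2-year WOMAC test uses one change score per patient, so it leaves out drop-outs and makes no use of the interim WOMAC scores already collected

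*Protocol article*

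**What the plan says.** All references are to the protocol article.

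- **Objectives.** The primary objective is to "compare the total Western Ontario and McMaster Universities Arthritis Index (WOMAC) score in MA TKA versus FA TKA at 2 years after surgery".
- **Statistical analysis.** Differences between the arms "will be analysed by calculating the difference from baseline per patient", with a 95% confidence interval for the difference in change. The methods listed for a continuous outcome are t tests and analysis of variance, with Mann–Whitney as the fallback. No repeated-measures model and no imputation rule is named.
- **Outcomes.** WOMAC is recorded before surgery and at 6 weeks, 6 months, 1 year and 2 years.
- **Sample size.** The 100 patients are justified "accounting for an expected drop-out rate of 10% during the 2-year follow-up period".
- **End-of-protocol treatment.** For patients who withdraw, are lost or die: "Data to the point of discontinuation will be used for analysis". The section does not say which analysis receives these data, or by what method.

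**The concern.** A patient who leaves after the 6-week, 6-month or 1-year visit has no 2-year change score. A test on that single score can only omit the patient, and the WOMAC scores that the patient did provide then carry no weight in the primary result. Those scores are informative, because they show how the patient was recovering before leaving.

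Two things are at stake. If the patients who leave differ from those who stay, and differ in different ways in the two arms, the completer comparison estimates the wrong quantity. If they do not, the comparison is still valid but uses less information than the trial collects. Enlarging the sample for drop-out answers the loss of numbers. It does not answer selective loss.

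**Working it through.** **1. The plan's own figures.** Sample size gives WOMAC means of 26 (SD 22.6) and 15 (SD 20.3), 90% power, two-sided 5%, 10% drop-out and 100 patients.
- Difference: 26 − 15 = 11, as stated.
- Pooled SD: √[(22.6² + 20.3²)/2] = 21.48. Standardised difference: 11/21.48 = 0.512.
- Exact t test at 90% power: 82 per arm, 164 evaluable, 164/0.9 = 182.2, so 183 in total.

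The stated 100 is not reproduced. That is a separate issue and nothing below depends on it. The steps below take 100 patients, 10% loss, 11 points and the quoted SDs as given.

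**2. What omission costs if loss is unrelated to outcome.** 100 × 0.10 = 10 patients lost, leaving 45 per arm if loss is even. The plan gives no SD for the change score, so the 2-year SD stands in.
- SE = 21.48 × √(2/n): 4.30 at n = 50 and 4.53 at n = 45.
- Power for 11 points: about 72% at 50 per arm and 67% at 45.

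**3. When omission biases the result.** Lower WOMAC is better. Let m be the fraction lost in an arm, and k the number of points by which the lost patients' 2-year scores would be worse than the completers'. The completer mean is then the arm mean minus m·k. The bias in the MA − FA difference is

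B = m(FA)·k(FA) − m(MA)·k(MA).

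The documents give neither the split of losses nor k, so both are assumed:

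| Loss FA / MA | k in FA / MA | B (points) |
|---|---|---|
| 10% / 10% | 10 / 10 | 1.0 − 1.0 = 0 |
| 5% / 15% | 10 / 10 | 0.5 − 1.5 = −1 |
| 5% / 15% | 20 / 20 | 1.0 − 3.0 = −2 |
| 15% / 5% | 10 / 10 | 1.5 − 0.5 = +1 |
| 15% / 5% | 20 / 20 | 3.0 − 1.0 = +2 |
| 10% / 10% | −5 / 5 | −0.5 − 0.5 = −1 |
| 10% / 10% | −10 / 10 | −1.0 − 1.0 = −2 |

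Equal loss of similar patients gives no bias. Otherwise the sign depends on who leaves which arm.

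**4. Whether the interim scores remove the bias.** This was simulated with 50 per arm, a true effect of 11 and 10–11% drop-out. Assumed means were 55 at baseline, then 40/32/28/26 (MA) and 36/24/18/15 (FA). SDs ran from 18 to 21.5, with correlation 0.75 between adjacent visits and 0.4 with baseline. Drop-out depended on the last observed WOMAC, with poor MA patients and well FA patients leaving. Three runs gave:

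| Dependence | Completer change score | All visits |
|---|---|---|
| Moderate | 9.8 to 10.0 | 10.9 to 11.0 |
| Strong | 9.0 to 9.3 | 10.9 to 11.1 |

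The completer bias is 1.0 to 2.0 points towards no effect, and the all-visit analysis is close to 11. When drop-out did not differ by arm there was no material bias. The SE was then about 4.6 for completers and 4.0 to 4.2 for all visits.

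**5. Where that precision gain comes from.** Take the ends of the assumed SD range: 18 at baseline and 21.5 at 2 years.
- Change score: SD = √(18² + 21.5² − 2 × 0.4 × 18 × 21.5) = √476.65 = 21.83. SE at 45 per arm = 21.83 × √(2/45) = 4.60.
- Baseline as covariate: SD = 21.5 × √(1 − 0.4²) = 19.71. SE at 45 per arm = 4.15. With no loss (50 per arm) it is 3.94.

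Baseline adjustment accounts for the step from 4.60 to 4.15. Recovering the drop-outs can add at most the step from 4.15 to 3.94. The interim scores matter mainly for bias.

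**The case against.** **The sentence on discontinued patients need not refer to the 2-year test.** It is met if their data serve the earlier-visit, radiological and complication analyses. This stands. A reader might infer that omitting drop-outs from the 2-year test contradicts that sentence. It does not, because the sentence does not name the analysis. What remains is that the role of these data in the primary comparison is unstated.

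**No last score is carried forward.** A reader might also infer that the plan would put a mid-recovery score in place of the 2-year score. Nothing in the article says so. Sizing for drop-out and a per-protocol primary set both point to completers. Any bias or inflated type I error calculated for carry-forward is therefore not a property of this plan.

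**Arm-specific drop-out is assumed.** Patients and outcome observers are blinded, which makes arm-specific reasons for leaving less likely, and the documents give no evidence of them. The simulated drop-out depends only on observed scores, which favours the likelihood model by construction. Both points stand, so the bias is conditional. It is also modest: 1 to 2 points against an SE of about 4.5.

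**Missing-data rules belong in the analysis plan.** Their absence from a condensed article is no fault. But the article does fix the form of the comparison, and a better form is available from the same data. Nor does listing analysis of variance rescue it: the text ties the comparison to one difference per patient, and classical repeated-measures analysis of variance drops incomplete cases as well.

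**Conclusion.** The point holds as a low-cost improvement to the primary analysis. The stated 2-year comparison leaves out the roughly 10% of patients expected to lack a 2-year WOMAC, and gives no weight to three post-operative WOMAC scores that are collected anyway.

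If drop-out depends on earlier scores differently by arm, the completer estimate can be off by about 1 to 2 points on an 11-point target, in either direction. That size rests on assumed means, correlations and drop-out mechanisms, not on figures in the documents. If drop-out works alike in both arms, the cost is precision only: an SE of about 4.6 against 4.0 to 4.2 under the same assumptions, most of that difference being due to baseline adjustment.

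The documents do not show that the primary result will be biased, nor that the plan's passages conflict.

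**What to change.** 1. **Statistical analysis.** Analyse total WOMAC with one likelihood-based repeated-measures model using the 6-week, 6-month, 1-year and 2-year scores. Include arm, visit, arm-by-visit and baseline WOMAC by visit, with an unstructured covariance. The primary result is the 2-year arm contrast with its 95% confidence interval.
2. **End-of-protocol treatment.** State that WOMAC scores obtained before discontinuation enter the primary comparison through this model, and that no single value is carried forward.
3. **Sensitivity analysis.** Shift the unobserved 2-year scores by a stated range, separately by arm, and report how the contrast changes.

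The cost is a few sentences and a standard mixed model in the software already named. No new data or visits are needed. The downside is that the model assumes drop-out depends on observed scores; the third step tests how far the result relies on that. Which population is primary is a separate question, and this change does not settle it.
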